## Abstract

**Background:**

The increasing rate of mental health issues among adolescents has recently been a considerable concern in Hong Kong. In particular, adolescents with low socioeconomic status (SES) are likely to experience poor mental health, including low self-esteem and high levels of anxiety, anger, and depression. Previous research has found that physical activities have a positive impact on improving mental health outcomes among adolescents. However, approximately 96% of adolescents in Hong Kong do not engage in regular exercise, which potentially increases the risk of poor mental health.

**Objective:**

In this study, we aim to examine whether changes in the 3 indicators (reduced ill-being, enhanced well-being, and cognitive functions) of mental health among adolescents with low SES are evident before and after exercise. In addition, this study compares the effectiveness of aerobic exercise and high-intensity interval training on these indicators among adolescents with low SES.

**Methods:**

A total of 78 participants from low-income families aged between 12 and 15 years from 3 to 4 secondary schools will be recruited for this study. They will be randomly assigned to either an aerobic exercise group (26/78, 33%), a high-intensity interval training group (26/78, 33%), or a control group (26/78, 33%). Participants in the first 2 groups will take part in a 10-week training program period. Participants in the control group will participate in other physical activities during the same intervention period. The training sessions will be conducted 3 times per week on nonconsecutive days. A range of neuropsychological tests and psychometric scales will be used to measure the executive functions and indicators of psychological well-being and ill-being, including enjoyment, self-efficacy, mood, depression, anxiety, and stress at pretest, posttest, and follow-up assessments.

**Results:**

The project was funded in 2021 by the Research Matching Grant Scheme, through the University Grants Committee of the Hong Kong Special Administrative Region Government. Ethical approval has been obtained from the author’s institution. Participant recruitment will begin in January 2022 and continue through to April 2022. Data collection and follow-up are expected to be completed by the end of 2022. The results are expected to be submitted for publication in 2023.

**Conclusions:**

The findings will help inform policy makers and practitioners in promoting the importance of physical exercise to enhance mental health.

**Trial Registration:**

ClinicalTrials.gov NCT050293888; https://clinicaltrials.gov/ct2/show/record/NCT05029388

**International Registered Report Identifier (IRRID):**

PRR1-10.2196/34915

## Introduction

### Mental Health in Adolescents in Hong Kong

Poor mental health among adolescents has serious implications for adult morbidity and mortality. Mental health involves the absence of mental illnesses and life satisfaction [1]. In Hong Kong, the mental health of adolescents has been a subject of considerable concern in recent years. A recent survey of 11,493 local citizens revealed that approximately 74% of adolescents aged <25 years exhibit moderate to high levels of depressive symptoms (eg, depression, anxiety, and stress), 41% of the adolescents exhibit moderate to high levels of posttraumatic stress symptoms, and 36% of the adolescents have both diagnoses [2]. However, previous research has demonstrated that poor mental health is unevenly distributed across different socioeconomic groups, with high clusters in families with a low socioeconomic status (SES) [3].

Families in this category are deprived in multiple ways and are affected by numerous stressors related to finances, social relations, employment opportunities, and physical illness compared with families from other socioeconomic groups [4]. For instance, adolescents with low SES often have worse access to education and social participation than their peers with an average or high SES [5]. In addition, the results from a meta-analysis study of 34 countries from 2002 to 2010 indicated that adolescents with low SES are affected by physical symptoms and have poor mental health, including low self-esteem and high levels of anxiety, anger, and depression [6]. In a sample of Chinese adolescents in Hong Kong, adolescents who grew up in families with a Comprehensive Social Security Assistance (CSSA) scheme had significantly higher levels of suicidal intention than those in families without CSSA [7].

### Interventions for Mental Health

Numerous mental health interventions are popular, but the scope of their effects is unclear. Costigan et al [8] stated that effective mental health interventions should address the following 3 indicators: (1) cognitive function, (2) well-being, and (3) ill-being. Conventional strategies such as cognitive behavioral therapy (CBT) [9] and dialectical behavior therapy (DBT) [10] are mainly based on therapeutic models. CBT focuses on challenging and changing dysfunctional thoughts, and DBT encourages clients to accept and validate their feelings [9]. Although the results in terms of reducing clinical symptoms are promising, their effectiveness in enhancing overall well-being is debatable. Moreover, one has to commit themselves to the process to benefit from CBT or DBT; these strategies may not be suitable for individuals with low capacity to change themselves (their thoughts, feelings, and behaviors). Moreover, school-based prevention programs [11] and web-based self-help interventions [12] are commonly used as preventive measures in school settings. School-based programs are implemented in schools to minimize high-risk behaviors [11]. Web-based self-help interventions allow individuals to work in their own time and use web-based resources to assist with their problems [12]. Similar to conventional strategies, the effectiveness of these intervention programs relies heavily on an individual’s motivation and capacity. Individuals with low SES often perceive themselves as incompetent, and this stigma contributes to their low motivation to change [13]. Furthermore, several studies have criticized that prevention programs fail to target the enhancement of mental health among *at-risk* students and to train school personnel, such as teachers and social workers, to identify these students [14]. Therefore, physical exercise is presently considered as an effective intervention because of its safe, nonpharmacological, and cost-effective nature [15] that can provide a range of health benefits, including improvements in body composition and physical capacity, among individuals [16]. Recent evidence has confirmed that physical exercise has a positive effect on mental health outcomes for youth through physiological and psychological pathways [17].

### Previous Research on Physical Exercise

#### Physiological Evidence

Studies that are focused on physiological evidence have commonly demonstrated a direct positive effect of physical exercise on individuals’ neurological processes, thereby indicating that cardio activities are directly and immediately beneficial to mental health. Two main research streams that cite physiological evidence, namely, those that focus on monoamines and those that focus on endorphins, are present. The first research stream reveals that physical activity upregulates the synaptic transmission of monoamines, including the 3 major neurotransmitters, namely, norepinephrine, dopamine, and serotonin [18]. A similar effect has been found for antidepressant drugs [19], although exercise has been proven to be as effective as antidepressants for alleviating depressive symptoms among patients with major depression [20]. The hypothesis regarding endorphins is also popular for explaining the impact of aerobic exercise on mental health. Several researchers have believed that endorphins may lead to energy conservation during exercise and consequently exhibit psychological effects, such as improved mood states and reduced anxiety [21]. Direct evidence stating that physical activity can elevate plasma endorphin levels also exists [22].

#### Psychological Evidence: 3 Mental Health Indicators

Although physiological evidence has established a direct association between physical activity and mental health, researchers are also keen to identify how physical activities may benefit mental health. Several researchers have conducted studies based on the three indicators of mental health that were proposed by Costigan et al [8]: (1) cognitive function, (2) well-being (eg, enjoyment), and (3) ill-being (eg, depression and negative affect).

With regard to cognitive function, growing evidence indicates that participating in exercise positively affects the executive functions [23]. Executive function is an umbrella term that covers a wide array of cognitive processes that govern goal-directed actions and adaptive responses to novel, complex, or ambiguous situations [24]. Numerous studies have found that intense physical exercise improves working memory [25], inhibitory control [25], and cognitive flexibility in typical [26] and low-income adolescents [27].

Physical exercise has been associated with improved well-being, including life satisfaction and self-esteem [8]. Exercise is a challenging activity, but the process of engaging in exercise could provide individuals with a meaningful experience of mastery that may lead to improved mood states and self-confidence [28]. Affect regulation theory suggests that exercise could regulate affect by reducing negative mood states and enhancing positive mood states that are conducive to mental well-being [29-31]. Furthermore, as described in the relevant literature, exercise can divert an individual from unfavorable stimuli (eg, worries, stress, and depressive thoughts), leading to improved mood [32,33].

Physical exercise has also been associated with reduced ill-being. A meta-analysis of 73 studies confirmed that increased levels of physical activity significantly reduced depression, anxiety, psychological distress, and emotional disturbance among children [34]. Archer and Garcia [35] found that regular physical exercise ameliorated the symptoms of anxiety and depression. Behavioral activation theory posits that depressive symptoms may be alleviated when individuals replace passive activities with exercise and other entertaining activities [36].

### Exercise Regimen

Although a lack of consensus regarding the most effective training regimen for physical exercise is evident in clinical review studies from 2000 to 2014, Ranjbar et al [37] have recommended the following components of an effective exercise program to benefit adolescents with poor mental health. On the basis of the frequency, intensity, time, and type principle, an exercise program should include the following characteristics: (1) structured aerobic exercise, which requires the heart to pump oxygenated blood for delivering oxygen to working muscles and stimulates an increase in the heart rate (HR) and breathing rate [38]; (2) group exercise, particularly for adolescents; (3) low (40%-55% maximal oxygen consumption) to moderate (65%-75% maximal oxygen consumption) intensity exercise; (4) 45- to 60-minute exercise sessions; (5) exercise frequency of at least three to four sessions per week, which is equal to ≥150 minutes of exercise per week; and (6) an exercise duration equal to ≥10 weeks.

Overall, extensive research has confirmed that physical exercise can significantly improve physical and mental health, whereas aerobic exercise has been the main focus of most previous studies. Recent studies have attempted to determine whether low-volume high-intensity interval training (HIIT) could be a time-efficient exercise strategy for improving health and fitness among the general population.

### High-Intensity Interval Training

HIIT is a time-efficient type of aerobic training that involves a short duration of full-effort exercise, followed by a rest period. HIIT is mainly appealing because it can be completed in a relatively short period and results in physiological adaptations that are equivalent to long sessions of traditional aerobic training and improvements in physical and mental health. This strategy may be feasible and effective for increasing physical health outcomes among young people [39,40]. Compared with low-intensity, high-volume (duration) endurance aerobic training (ie, cycling), HIIT can result in better oxygen uptake, greater muscle deoxygenation, and better exercise performance [41]. A previous study also revealed that patients participating in high-intensity interval running reported higher perceived enjoyment than those participating in moderate-intensity continuous running [42]. A pilot study of a 10-week HIIT program resulted in improved metabolic outcomes among patients with schizophrenia, thereby supporting the benefits of HIIT for physical fitness and mental health. Furthermore, studies have also shown that HIIT reduces distress and anxiety [43].

Despite the promising evidence that supports the adoption of HIIT among adults with various conditions, limited research that targets adolescents, particularly those with low SES, is available [39,40]. High-intensity activities performed in short, repeated bouts with periods of recovery in-between could be an achievable and enjoyable alternative to high-volume continuous exercise for adolescents, including *low-active* adolescents [40,44].

### Research Gaps and Study Objectives

The conditions and ability of poor individuals to manage and potentially escape poverty are the core of policy agendas and ethical and economic concerns among societies. Behavioral research has recently been applied to policy-relevant challenges and has explored the significant potential of simple interventions to influence cognition and behavior [45]. Poor individuals, particularly young poor individuals in Hong Kong, have received little attention as part of this endeavor despite their characteristics that satisfy the qualifications of clear candidates for interventions that could improve disadvantaged situations.

Although several longitudinal studies have confirmed that growing up in a disadvantaged family is a significant risk factor for poor mental health, numerous research gaps should be addressed by further investigation. For instance, most studies on mental health and socioeconomically disadvantaged adolescents have been restricted to understanding and confirming the link between mental health and SES. Research that aims to examine whether mental health can be enhanced through physical exercise is scarce. However, such research would be extremely useful for expanding early interventions. To date, a steady decline in the number of physically active students in Hong Kong is evident. Furthermore, the situation among adolescents in Hong Kong is worse, given that 96% of them are insufficiently active [46]. Hence, there is a considerable need for this kind of research to arouse public awareness of the link between physical activity and mental health. Although previous studies have reported improvements in the mental health of adolescents after exercise sessions, a lack of follow-up data is available on assessing the sustainability of exercise intervention with moderate intensity over a long duration. In addition, relatively few studies have directly compared the effects of aerobic exercise and HIIT on the mental health of adolescents with low SES. Given that HIIT training has become popular and effective in improving health and well-being, HIIT exercise should be used as the comparison group to examine the effectiveness of traditional aerobic exercise.

Following the health benefits of regular exercise and the limited research on exercise-based interventions (aerobic exercise vs HIIT) in low-SES adolescents, this study primarily aims to investigate the effectiveness of aerobic exercise and HIIT on the 3 indicators of mental health among low-SES adolescents. This study particularly intends to answer the following two research questions: (1) Is there any change in the 3 indicators of mental health (ie, cognitive function, well-being, and ill-being) before and after exercise? and (2) Which exercise regimen (aerobic exercise or HIIT) is more effective in reducing ill-being and enhancing well-being and cognitive function among adolescents with low SES?

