## Methods

### Overview

Participants will be randomly assigned to an aerobic exercise group, an HIIT group, or a control group. Participants in the first 2 groups will partake in a 10-week training program, conducted 3 times per week on nonconsecutive days. Participants in the control group will participate in other physical activities during the same intervention period.

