### Study Design

A randomized controlled trial will be used to examine the effects in individuals who are assigned to either a 10-week aerobic exercise training group, a 10-week HIIT training group, or a control group. A total of 78 secondary school adolescents will be recruited for this study. Subsequently, the adolescents will be randomly clustered in a controlled intervention trial. The effectiveness of the intervention will be assessed through a pretest, posttest, and a follow-up design that will be evaluated based on the degree of improvement in performance across the 3 time points. If any important protocol modifications are made, all relevant parties will be informed. These include the trial registry, human research ethics committee, research team members, all participating students and their parents, the journal that publishes the study protocol, and the funding body.

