### Data Analysis

Interim analysis will not be performed, and data analysis will only begin after the follow-up stage. The PI and trained research assistants will have access to the final trial data set. Data will be analyzed using SPSS version 26. A missing value analysis procedure will be conducted to detect the missing values in the data file. The demographic characteristics of the participants will be investigated using the chi-square test for independence (for nominal variables) and 1-way ANOVA (for continuous variables). A Bonferroni post hoc test will subsequently be conducted for group comparisons. To examine the changes between and within groups for each outcome measure (ie, self-efficacy, mood, enjoyment, working memory, cognitive flexibility, inhibition, depression, anxiety, and stress), a 3 (before intervention vs after intervention vs follow-up) × 3 (aerobic exercise vs HIIT vs control) repeated-measure ANOVA will be conducted. A post hoc analysis will be used to confirm whether significant differences for any of the outcome variables exist among the groups. The Bonferroni method will be used to adjust the *P* values.

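### Research question 1 and the effectiveness criterion are worded as before-after change with no comparator; a baseline-adjusted contrast with control should be named as the test

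*Protocol article*

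**What the plan says.** All references are to the protocol article.

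- **Abstract, Objective:** the study asks whether changes in the three indicators "are evident before and after exercise".
- **Research Gaps and Study Objectives:** the general aim is wider: "this study primarily aims to investigate the effectiveness of aerobic exercise and HIIT on the 3 indicators of mental health". It is then narrowed to two questions. The first is "1) Is there any change in the 3 indicators of mental health (ie, cognitive function, well-being, and ill-being) before and after exercise". The second asks which of the two regimens works better. Neither asks about exercise against control, although 26 of 78 participants are randomised to control.
- **Study Design:** the effectiveness of the intervention will be "evaluated based on the degree of improvement in performance across the 3 time points". No contrast with control is mentioned.
- **Overview:** "Participants in the control group will participate in other physical activities during the same intervention period".
- **Data Analysis:** "To examine the changes between and within groups for each outcome measure", "a 3 (before intervention vs after intervention vs follow-up) × 3 (aerobic exercise vs HIIT vs control) repeated-measure ANOVA will be conducted". This is followed by "A post hoc analysis will be used to confirm whether significant differences for any of the outcome variables exist among the groups", with Bonferroni adjustment. Pretest is one of the three levels of the time factor, and no baseline covariate is stated. The section does not say whether time, group or their interaction answers either question, nor at which visit the groups are compared.

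**The concern.** A change over time within an arm is the sum of any exercise effect and everything else that happens over the period. Here that includes practice on the Stroop, Digit Span and card-sorting tests, each taken at pretest, posttest and follow-up, and calendar effects such as the school term or the pandemic. The randomised control arm is there to remove these. Read literally, question 1 and the effectiveness criterion are answered without it, so a positive answer could be reported when exercise has done nothing.

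A second and separate issue is precision. In the planned model pretest is an outcome, so group comparisons are in effect comparisons of change scores. With randomised arms, adjusting the later score for the pretest score gives a smaller variance from the same data, which matters with about 21 completers per arm.

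**Working it through.** **Inputs from the article (Participants).** f = 0.25, alpha 0.05, 45 participants required before inflation, 26 per arm recruited, 20% attrition. Completers per arm: 26 × 0.8 = 20.8, taken as 21, so 42 in the two exercise arms and 63 in all.

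**Assumptions, not in the article.** Correlation rho between visits 0.3, 0.5 or 0.7; a gain of 0.2 to 0.3 SD common to all arms; a true exercise effect of d = 0.5 for the power figures.

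**Step 1: does the sample size show which effect is meant?** For the interaction, lambda = f² × N × m / (1 − rho), with 3 groups and m = 3 visits. At N = 45 and rho = 0.5, lambda = 0.0625 × 45 × 3 / 0.5 = 16.9 on 4 and 84 df, and power is 0.91. The smallest N for 90% is 44, or 45 in equal arms. The time effect at 95% power also leads to 45 (43, rounded up to equal arms). Neither power nor rho is stated, so 45 fits either effect and does not settle the matter.

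**Step 2: before-after tests with no exercise effect.** In SD units the SD of change is √(2(1 − rho)), which is 1.0 at rho = 0.5. The paired t test has noncentrality gain × √n / √(2(1 − rho)). For n = 21, gain 0.3 and rho 0.5 this is 0.3 × √21 = 1.37.

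| Test | rho | Gain 0.2 SD | Gain 0.3 SD |
|---|---|---|---|
| One exercise arm, n = 21 | 0.3 | 11% | 20% |
| | 0.5 | 14% | 26% |
| | 0.7 | 20% | 39% |
| Both exercise arms, n = 42 | 0.3 | 19% | 36% |
| | 0.5 | 24% | 48% |
| | 0.7 | 37% | 69% |

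If the shared gain is 0.3 SD at both later visits, the time main effect of the 3 × 3 ANOVA with 21 per arm is significant in 68% (rho 0.5) to 89% (rho 0.7) of simulated trials. The group-by-time interaction in the same simulations is significant in about 5%.

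**Step 3: precision.** For a posttest contrast between two arms, the variance per participant is 2(1 − rho) on change scores and 1 − rho² after baseline adjustment. The ratio is (1 − rho²) / (2(1 − rho)) = (1 + rho)/2, that is 0.65, 0.75 and 0.85 at rho 0.3, 0.5 and 0.7.

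For 21 versus 21 at d = 0.5 and rho = 0.5, the noncentrality is 0.5 / √(1.0 × 2/21) = 1.62 on change scores and 0.5 / √(0.75 × 2/21) = 1.87 adjusted.

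| Alpha | Change score | Baseline-adjusted |
|---|---|---|
| 0.05 | 35% | 45% |
| 0.05/3 = 0.0167 (Bonferroni, three pairwise comparisons) | 20% | 28% |

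**The case against.** The strongest reply is that this is a randomised trial with a concurrent control, and that the planned model is a controlled one. It has a group factor, hence a group-by-time interaction, and post hoc comparisons among the groups. The aim stated just before question 1 speaks of effectiveness, and the article is condensed, so the decisive contrast may be named in an analysis plan that is not shown. Much of this stands. A reader might infer that the trial tests exercise only by before-after change; Data Analysis does not support that, and the interaction holds its error rate under a shared gain. What remains is not an omitted detail. It is the wording of the question and of the effectiveness criterion, which point away from the control arm and leave the time effect available as the answer.

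A reader might also infer that having pretest as an outcome level causes practice effects to be credited to exercise. It does not; it costs precision only. Nor do the documents support regression to the mean as a further explanation, since eligibility rests on age and household income and not on an extreme outcome score.

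On precision, the interaction is a valid test, and the gain from adjustment depends on a correlation that the article does not give: at rho = 0.7 the variance falls by only 15%. The adjusted pairwise contrast is not more powerful than the planned test in every respect. Under Bonferroni over three comparisons it has 28% power, against about 35% for the 4-df interaction at the same rho if both regimens have d = 0.5 at both later visits. The like-for-like gain is over the same pairwise contrast on change scores.

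Finally, the control activity is stated openly and is not an error. It only limits what the comparison can be said to show.

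**Conclusion.** The point holds as one of framing and of an unnamed test. The research question, the abstract objective and the effectiveness criterion name no comparator, neither question asks exercise versus control, and the analysis text does not fix which effect answers question 1. If a before-after result is used, the chance of a false positive answer is 14% to 26% in one exercise arm and 24% to 48% in both arms combined, assuming a shared gain of 0.2 to 0.3 SD and correlation 0.5. If the interaction is used, it is about 5%.

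The loss of precision is separate and moderate: a variance ratio of 0.65 to 0.85 over correlations 0.3 to 0.7, and about 8 to 10 percentage points of power for a pairwise contrast at d = 0.5 and rho = 0.5. The sizes rest on assumed values of the gain, the correlation and d. The variance formula and the ambiguity in the text do not depend on those values.

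**What to change.** - Reword question 1, the abstract objective and the effectiveness criterion to ask whether each exercise regimen improves the outcomes compared with the control group, at posttest (main) and at follow-up.
- Name the test. Answer questions 1 and 2 by planned between-group contrasts of the posttest and follow-up scores, adjusted for the baseline score of the same measure, keeping the Bonferroni adjustment already planned. If the 3 × 3 ANOVA is retained, state that the group-by-time interaction, and not the time effect, is the basis for any claim about exercise.
- Label within-group changes as descriptive.
- Word conclusions as effects relative to the other physical activities of the control group.

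The cost is a few sentences in the objectives and analysis sections. Baseline scores are already collected and no design change is needed. Because the article says that analysis starts only after follow-up, the wording can be settled before any outcome data are analysed.
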